### Sample size justification

The sample size calculation is based on the test of the null hypothesis that the mean reductions in RNLI scores in the two populations (intervention and control) are equal. The primary measure of effect is the change in RNLI scores from baseline to 12 weeks (two-tailed type I error of 0.05; type II error of 80%). The criterion for significance (alpha) has been set at 0.05. The test is two-tailed, which means that an effect in either direction will be interpreted. The sample size of 105 per group was calculated using an a priori sample size calculator for Student’s t-tests [91]. With the proposed sample size of 105 in each of the two groups (i.e. assuming a 1:1 allocation ratio), the study will have power of 80% to yield a statistically significant result using a t-test (assuming an intention-to-treat principle for the analysis) of the difference between mean changes in RNLI scores (12 weeks to baseline) at alpha = 0.05. This computation assumes that RNLI change scores are normally distributed, the mean difference is 3.1 (95% confidence interval [CI] = -3.37–9.56) (corresponding to mean changes of 6.26 [for the intervention group] vs 3.16 [for the control group]) and the common within-group standard deviation is 3.23 These estimates are modified estimates from our pilot trial, which account for the type of intervention planned for in this study. We calculated the sample size to address the primary outcomes. Table 1 provides the sample sizes for different values of the expected plausible difference and standard deviations.

**Table 1 Tab1:** Sample sizes for different plausible values of the mean difference and corresponding standard deviations

SD	1.0	2.0	3.0	4.0
3.0	292	76	38	20
4.0	506	128	60	24
5.0	788	200	90	52
6.0	1230	352	128	74
7.0	1604	404	182	100
8.0	1806	506	220	128
9.0	2598	652	292	200

Fixed α = 0.02 B = 0.05

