To allow for subgroup analysis, and to control for factors of age and function, as well as balancing of the number of participants between the groups at the three sites, we chose a sample size of n = 182 (i.e. 91/group), which corresponds to a minimal clinically important difference of 3. This difference was selected because it is plausible and feasible to achieve as shown by our pilot study, and it is associated with a three-point clinically important improvement [92]. This sample size (91/group) would also provide 80% power to detect time by treatment interaction. Thus, with 30 participants per group for each of the three sites, and to account for dropouts (20%), the planned total sample size is (30 × 3 sites) (20%) × 2 groups = 216 participants, or 108 participants per group.

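### The sample size justification does not hold together: 105 per group does not follow from its stated inputs, 91 rests on an unexplained SD of 7, the dropout allowance leaves about 86, and Table 1 is mislabelled and partly wrong

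*Protocol article*

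**What the plan says.** All of this is in the protocol article under Sample size justification.

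- **First size.** "The sample size of 105 per group was calculated using an a priori sample size calculator for Student’s t-tests". The inputs are a difference of 3.1 in mean RNLI change (6.26 vs 3.16, 95% CI -3.37 to 9.56), a within-group SD of 3.23, 1:1 allocation and two-tailed alpha 0.05. With 105 per group, "the study will have power of 80% to yield a statistically significant result using a t-test". The error rates are also written as "two-tailed type I error of 0.05; type II error of 80" per cent. The inputs are described as modified from the pilot trial.
- **Table 1.** It gives sample sizes for SDs 3 to 9 and differences 1 to 4, with the footnote "Fixed α = 0.02 B = 0.05".
- **Second size.** "To allow for subgroup analysis, and to control for factors of age and function", and to balance numbers across sites, "we chose a sample size of n = 182 (i.e. 91/group), which corresponds to a minimal clinically important difference of 3". The 91 per group is also credited with 80% power for the time-by-treatment interaction.
- **Enrolment.** The 91 becomes 30 per group at each of three sites, and "the planned total sample size is (30 × 3 sites) (20%) × 2 groups = 216 participants", or 108 per group.

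**The concern.** Two per-group sizes, 105 and 91, are each tied to 80% power and nothing reconciles them. The second is smaller than the first, yet it is introduced as making room for subgroup analysis and covariate control. Allowing for subgroup tests cannot justify a smaller trial.

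The SD in the text (3.23) is not the SD behind either size. The dropout step multiplies where it should divide. The table's stated error rates are not those of the text.

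At stake is whether anyone can say what power 216 participants give on the primary outcome. That turns entirely on the SD of RNLI change, and the section implies three different values for it.

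**Working it through.** Unless noted, sizes are for a two-sample t-test at two-sided alpha 0.05 and 80% power, computed exactly with the noncentral t. The normal approximation is n per group = 2 × [(1.960 + 0.842) × SD / difference]².

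**1. The 105 per group.** With difference 3.1 and SD 3.23, n = 2 × (2.802 × 3.23 / 3.1)² = 17.04, so 18 per group, or 19 by the exact t. The plan's figure does not reproduce. One- and two-sided tests, alpha from 0.01 to 0.05 and power up to 95% never gave more than 39. Solving backwards, SD = 3.1 × √(105/2) / 2.802 = 8.02 (exact t: 7.98).

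**2. The 91 per group.** In the difference-3 column of Table 1, 182 appears only in the SD 7 row. For that cell the exact t gives 174 in total (normal: 172), so 182 is 8 too high.

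**3. Dropout.** 30 × 3 × 1.2 = 108 per group, and 2 × 108 = 216, so the plan's total reproduces as n × (1 + 0.20). A 20% loss then leaves 108 × 0.8 = 86.4 per group. Dividing by 0.8 instead:

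| Completers wanted per group | Enrol per group | Total |
|---|---|---|
| 90 | 113 | 226 |
| 91 | 114 | 228 |
| 105 | 132 | 264 |

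**4. Table 1.** I read the entries as total N, since 182 is glossed as 91 per group. At alpha 0.02 and beta 0.05 no cell matches; SD 7 with difference 3 would need 348. At two-sided 0.05 and 80% power the SD 5 row matches exactly (788, 200, 90, 52), so this is the basis of the table. Even so, 16 of 28 cells differ from the exact value. Nine differ by more than 3% and more than 2 participants:

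| SD | Difference | Printed | Exact |
|---|---|---|---|
| 3 | 3 | 38 | 34 |
| 4 | 4 | 24 | 34 |
| 6 | 1 | 1230 | 1134 |
| 6 | 2 | 352 | 286 |
| 7 | 1 | 1604 | 1542 |
| 7 | 2 | 404 | 388 |
| 7 | 3 | 182 | 174 |
| 8 | 1 | 1806 | 2012 |
| 9 | 4 | 200 | 162 |

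Two of these are too small: 24 gives 65% power and 1806 gives 76%.

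**5. Where 3.23 may come from.** The CI half-width is (9.56 + 3.37)/2 = 6.465. The pilot had 61 participants (33 and 28; Missing data section), so 59 df and t = 2.001. Then 6.465 / 2.001 = 3.23, which is the printed SD. On this reading 3.23 is the standard error of the pilot difference, and the SD is 3.231 / √(1/33 + 1/28) = 12.6. With the 31 and 24 who had 12-week data (53 df), the standard error is 3.22 and the SD is 3.223 / √(1/31 + 1/24) = 11.9. For a difference of 3.1, those SDs need about 259 or 230 per group (normal approximation).

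**6. Power at 86 per group.**

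| Basis | Power |
|---|---|
| Difference 3.1, SD 3.23 (as printed) | above 99.9% |
| Difference 3, SD 7 (behind 91) | 79.8% |
| Difference 3.1, SD 7.98 (implied by 105) | 72% |
| Difference 3.1, SD 11.9 to 12.6 (if 3.23 is a standard error) | 40% to 36% |

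**7. Subgroups (illustration).** Assume SD 7, an interaction of 3 points and 91 per group. The standard error is 7 × √(2/(91f) + 2/(91(1 − f))), where f is the share in one subgroup. Power is about 30% at f = 0.5 and 24% at f = 0.25. The interaction size and the splits are my assumptions.

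**The case against.** **Power need not be short.** A reader might infer that 216 fails to deliver 80% power. The documents do not support that as a flat statement. On the basis that produced 91 per group, 86 completers still give 79.8%, and at the printed SD power is above 99.9%. The 72% needs an SD solved back from 105, and the 36–40% needs an inference about 3.23. Nor is 86 a third target; it follows from the plan's own dropout rate.

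**The planned analysis is kinder than a completer t-test.** It uses multiple imputation and adjusts for baseline RNLI, which usually improves precision. Pilot loss at 12 weeks was 6 of 61, about 10%; at that rate 108 leaves about 97 per group, more than 91. This stands, but it does not mend arithmetic that states 20%.

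**Many table discrepancies are rounding.** Cutting or rounding the effect size to two decimals reproduces 9 of the 16 discrepant cells, and one decimal reproduces 352 and 200. The number 105 is the answer for an effect size of 0.39, and 1806 may be 1860 with digits transposed. This is a plausible, mostly conservative explanation. The rounding is inconsistent, however, and it explains neither 24 nor the footnote.

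**No power is claimed for subgroups.** That is true, and the interaction tests are properly specified. The point is only that moving from 105 to 91 cannot be presented as allowing for them.

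**Conclusion.** The justification is wrong as written, whichever SD is true. The 105 does not follow from 3.1 and 3.23; 105 and 91 are unreconciled; the inflation leaves about 86 per group, short of 90, 91 and 105; the Table 1 footnote is wrong, as are nine cells materially; and the type II error should read 20%.

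The effect on power is not settled. At 86 per group it ranges from about 80% through 72% to 36–40% across the SDs of about 7, 8 and 12 that the section implies. The last case rests on reading 3.23 as a standard error. The numerical match is close, but the article calls its inputs modified pilot estimates, so only the sponsor can confirm it. These powers are for a completer t-test and take no credit for imputation or baseline adjustment.

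**What to change.** 1. Confirm the SD of RNLI change from the pilot data, and whether 3.23 is an SD or a standard error. Do this before any sentence is deleted, because the first paragraph holds the figures that raise the question.
2. State one basis: one SD, one difference, two-sided alpha 0.05. Reconcile or withdraw the 105 and 91 figures accordingly.
3. Restate the power that 216 enrolled gives with about 86 completers per group after 20% loss, without presuming that it stays near 80%.
4. Recompute Table 1, label it as total N at two-sided alpha 0.05 and 80% power, and correct the type II error to 20%.
5. Do not present 91 per group as sized for subgroup analysis; describe the subgroup interaction tests as exploratory.

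The cost is a look at existing pilot data, a recomputed table and some wording. The restated power may be little changed or, if the SD is about 12, much lower.

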#### Sampling for the qualitative data

The study will use purposeful criterion sampling to select persons participating in the FIT for FUNCTION program [93]. The sample size will be driven primarily by data saturation, as “collecting data until no new information is obtained” [94]. We will recruit 6–12 participants as recommended for phenomenological studies [95, 96], accounting for data saturation.

### Proposed methods for protecting against sources of bias

#### Contamination

Participants in the FIT for FUNCTION group will receive the intervention in a closed room at the YMCA three days/week. Persons in the control group who have a complimentary YMCA membership will self-determine the frequency of their attendance. Since the YMCA staff who interact with the intervention group will have no contact with the control group, and because the intervention will be delivered at a distance from routine programs, we anticipate there will be minimal opportunity for contamination.

#### Blinding

Independent assessors who are blind to group allocation will administer the study outcomes to the participants. The data analyst will also be blind to the group allocation.

#### Missing data

There are set timelines for administration of the outcomes and we will use multiple procedures to minimize missing data and loss to follow-up, such as repeated phone calls and mailed self-report assessments. In the pilot study, complete 12-week data were collected from 31 of 33 participants in the intervention group and 24 of 28 participants in the control group. Reasons for missing data included four participants who declined reassessment and two participants who we were unable to contact for follow-up. For the proposed trial, missing data will be assessed as to whether the pattern of missing scores is systematic or missing at random and we will use multiple imputation to perform the analyses.

### Data monitoring and auditing

This trial will not have a data monitoring committee and the study investigators will provide the auditing of the study since the estimated risk to the patients is low. The participants who undertake the research will be cleared to participate by a physician and determined to be medically stable and not at a high risk of mortality. The intervention of exercise and self-management and education have been studied with no serious adverse effects, so it is not expected that the participants will encounter any harm as a result of the intervention or control arm of the trial. There are no stopping rules or preliminary analyses planned.

### Analyses

The analysis and reporting of this trial will follow the CONSORT statement [97]. The baseline characteristics will be analyzed using descriptive statistics reported as mean (standard deviation [SD]) or median (first quartile [Q1], third quartile [Q3]) for continuous variables, depending on the distribution and count (percent) for categorical variables. All analyses of primary and secondary outcomes will follow the intention-to-treat principle. We will use multiple imputation to handle missing data [98]. The results will be reported as relative risk or odds ratio for binary outcomes or mean difference for continuous outcomes, with corresponding 95% CI and associated *p* value. All *p* values will be reported to three decimal places with those < 0.001 reported as *p* < 0.001. The criterion for statistical significance will be set at alpha = 0.05, adjusted using the Bonferroni method for multiple secondary outcomes. All analyses will be performed using Statistical Analysis Software 9.2 (Cary, NC, USA). Table 2 shows a summary of method of analysis for each outcome.

**Table 2 Tab2:** Variables, measures, and methods of analysis

Variable	Outcomes	Outcome measure	Methods of analysis
Primary objective: To compare the effects of a 12-week community-based YMCA wellness program specifically designed for people with stroke vs a standard YMCA membership on community integration at 12 weeks and 24 weeks			
Community integration	Community integration	RNLI	Generalized linear models (GLM)
Secondary objective: To compare the effects of a 12-week community-based YMCA wellness program specifically designed for people with stroke vs a standard YMCA membership on the following variables:			
(a) Physical activity	Physical activity	RAPA, accelerometry	GLM
(b) Physical functioning	Lower extremity performance, strength, walking speed, balance	SPPB, dynamometer; 6MWT, BBS	GLM
(c) Health-related QOL	Health-related QOL	EQ-5D-5L	GLM
(d) Cardiovascular health	Cardiovascular health	BP, HR, BMI, waist and hip circumference	GLM
(e) Cardiovascular health	Lipids, glucose, and inflammatory markers	HDL and LDL cholesterol, triglycerides, glucose, and glycated hemoglobin	GLM
(f) Self-management	Self-management	PAM	GLM
(g) Healthcare utilization and costs	Healthcare utilization and costs	CRF	Mann–Whitney U test
Subgroup analyses: sex differences in response to treatment; age group differences response to treatment	Sex differences response to treatment; age group differences response to treatment	Interaction term sex × treatment group; interaction term age group × treatment group	Regression analysis with interaction test between each subgroup variable and treatment group evaluating the credibility of subgroup findings using previously published criteria
Sensitivity analyses: to evaluate the effect of group that adheres to treatment			Regression analysis

In all analyses, results will be expressed as estimate of effect, corresponding 95%, and associated *p* values

All tests will be one-sided using alpha = 0.05 level of significance in accordance with the non-inferiority hypotheses

*RNLI* Reintegration to Normal Living Index, *RAPA* Rapid Assessment of Physical Activity, *SPPB* Short Physical Performance Battery, *6MWT* 6-min walk test, *BBS* Berg Balance Scale, *EQ-5D-5L* European Quality of Life 5-Dimension Questionnaire, *BP* Blood pressure, *HR* Heart rate, *BMI* Body mass index, *HDL* High density lipoprotein, *LDL* Low density lipoprotein, *PAM* Patient activation measure, *CRF* Case report form

To assess the effect of the intervention on RNLI (research question 1), physical activity levels, physical functioning, QOL, cardiovascular health, and self-management (research question 2), we will estimate group, time, and group × time interaction effects using generalized linear models for continuous variables. We will include relevant baseline variables as covariates in the analysis that differ between groups at baseline, notably time since stroke (TSS) if there is a significant between-group difference. We will also include the baseline score for the specific measure of interest. For example, for research question 1, the baseline score of the RNLI would be included as a covariate for evaluating post-program changes.Our hypothesis is that there will be reduced hospitalizations and physician visits for the intervention group compared to the control group (research question 3). Cost data are usually treated as non-parametric; therefore, a Mann–Whitney U test will be used to test relative ranks of participants between the groups on relative intervention cost.We will use prognostic indicators from participants’ profiles to determine factors associated with the greater benefit from the FIT for FUNCTION program (research question 4). These factors will be identified by expanding the models for the treatment effects on RNLI and function as the dependent variables, and using prognostic variables of co-morbidities, illness severity, depressive symptoms, mobility impairment and cognitive status, education, previous level of activity, stroke classification, and interactions involving age and gender, as independent variables in the regression models.

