#### Research questions and specific hypotheses

The proposed trial aims to answer the following research questions:Is the 12-week FIT for FUNCTION stroke program more effective than a standard YMCA membership in improving community reintegration (primary outcome) at 12 and 24 weeks?

*Hypotheses:* Participants in the FIT for FUNCTION group will demonstrate greater post-program improvement in community integration. Gains will be maintained at 24 weeks (12 weeks following program completion).2.Is the FIT for FUNCTION stroke program more effective than a standard YMCA membership in increasing levels of physical activity and improving physical functioning (walking, balance, strength), health-related QOL, cardiovascular health, and self-management at 12 and 24 weeks?

*Hypotheses:* Participants in the FIT for FUNCTION group will demonstrate greater post-program improvement in physical activity, physical functioning, health-related QOL, cardiovascular health, and self-efficacy. Gains will be maintained at 24 weeks (12 weeks following program completion).3.Is the FIT for FUNCTION program more cost-effective than a standard YMCA membership?

*Hypotheses:* Participants in the FIT for FUNCTION program will have lower direct and indirect medical costs over the 24 weeks of the trial period as evidenced by fewer hospital and physician visits, and formal and informal caregiver services. The costs associated with the FIT for FUNCTION program will be less than those for the control group. We also hypothesize that the FIT for FUNCTION program will be more effective in improving health-related QOL of participants.4.What participant characteristics are associated with degree of program response observed?

*Hypotheses:* Participants who demonstrate greater improvement in community integration (primary outcome) from the FIT for FUNCTION program will have less co-morbidities, illness severity, depressive symptoms, mobility, and cognitive impairment.

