#### Cardiovascular health

HR and BP will be measured after 5 min sitting at rest. BP will be measured at the brachial artery of the unaffected arm. Two measurements will be taken and averaged. If values differed > 5 mmHg, two more readings were done and the average taken across four readings [85]. HR and BP will also be measured at the end of the 6MWT as indicators of cardiovascular response during sub-maximal exercise. Body mass, height, and waist and hip circumference will be measured and body mass index and waist:hip ratio calculated. Blood samples will be collected following 12-h fast for lipid profile (total cholesterol, high-density lipoprotein cholesterol, low-density lipoprotein cholesterol, triglycerides), glucose (glucose, insulin, glycated hemoglobin), and inflammatory markers (C-reactive protein).

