#### Self-efficacy

Self-efficacy (SE) for physical activity will be assessed with a single question. Participants will be asked to rate how confident they are that they could participate in moderate intensity physical activity for 150 min per week on a scale of 1 (not confident) to 10 (very confident) [86]. Self-efficacy for managing chronic disease will be assessed using the Stanford Self-Efficacy for Managing Chronic Disease 6-Item Scale. This six-item scale is less burdensome for patients, containing items taken from several SE scales developed for the Stanford Chronic Disease Self-Management Program [87].

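### Secondary outcomes: Holm step-down would dominate the planned Bonferroni adjustment, and Table 2 and the text disagree on which outcomes are to be adjusted

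*Protocol article*

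**What the plan says.** **Method.** Under Analyses, the significance criterion is alpha = 0.05, "adjusted using the Bonferroni method for multiple secondary outcomes". Estimates are to be reported with ordinary 95% intervals. No family size and no adjusted threshold is given.

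**Blood markers.** Table 2, row (e), lists "HDL and LDL cholesterol, triglycerides, glucose, and glycated hemoglobin". The row label includes inflammatory markers, but none is among the five measures. The text under Secondary outcomes, Cardiovascular health, has a four-item lipid profile that includes total cholesterol, followed by "glucose (glucose, insulin, glycated hemoglobin), and inflammatory markers (C-reactive protein"), eight markers in all.

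**Self-efficacy.** The text under Secondary outcomes gives it its own heading and two measures: a single question on confidence in being active, and a scale ("Self-efficacy for managing chronic disease will be assessed using the Stanford Self-Efficacy for Managing Chronic Disease 6-Item Scale"). The hypothesis for research question 2 covers improvement in physical activity, "physical functioning, health-related QOL, cardiovascular health, and self-efficacy". Table 2 has no self-efficacy entry; row (f), self-management, names only the Patient Activation Measure.

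**Costs.** Objectives makes healthcare utilization and costs tertiary. Table 2 puts them in row (g) under the secondary objective, and the text describes them under Secondary outcomes.

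**Time points.** Research question 2 asks about 12 and 24 weeks. Objectives makes retention of benefits tertiary.

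**The concern.** There are two separate matters.

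The first is efficiency. The article fixes a single-step correction although a step-down version exists that needs no further assumption, protects the same error rate and can only reject more. Research question 2 spans many measures, so the threshold per test is severe and any free gain is worth having.

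The second is the list. A Bonferroni threshold is fixed entirely by the number of tests, and Holm depends on that number too. Analyses presents Table 2 as covering each outcome, yet it is not the set that the text calls secondary. If the list stays open, the threshold can be settled after results are known, and a reader cannot tell which one applied.

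**Working it through.** **No figure to reproduce.** The article states neither a divisor nor an adjusted alpha. The family sizes below are readings of the article, not its figures.

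**Step 1: count the family.**
- Rows (a) to (g) of Table 2: 7.
- Measures named in Table 2, with blood pressure and dynamometry each counted once: RAPA, accelerometry, SPPB, dynamometer, 6MWT, BBS, EQ-5D-5L, BP, HR, BMI, waist, hip, HDL, LDL, triglycerides, glucose, glycated hemoglobin, PAM and costs, which makes 19.
- Adding the five omitted (total cholesterol, insulin, C-reactive protein, two self-efficacy measures): 19 + 5 = 24.
- Counting 12 and 24 weeks separately: 2 × 19 = 38 or 2 × 24 = 48.

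**Step 2: threshold and power per test under Bonferroni.** Threshold = 0.05/m. For power, take 91 per group and a difference of 3 (Sample size justification), with SD 7 assumed because Table 1 shows 182 in total at that SD and difference. These are RNLI values and serve only as an illustration for the secondary outcomes. The non-centrality is (3/7) × √(91/2) = 2.89, and two-sided power ≈ Φ(2.89 − z), where z is the normal quantile at 1 − 0.05/(2m).

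| m | Threshold | Power per test |
|---|---|---|
| 1 (unadjusted) | 0.05 | 0.82 |
| 7 | 0.00714 | 0.58 |
| 19 | 0.00263 | 0.45 |
| 24 | 0.00208 | 0.43 |
| 38 | 0.00132 | 0.37 |
| 48 | 0.00104 | 0.35 |

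The thresholds span a factor of 48/7 ≈ 6.9.

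**Step 3: why Holm dominates.** Order the p values and compare the smallest with 0.05/m, the next with 0.05/(m − 1), and so on, stopping at the first failure. Every threshold is at least 0.05/m, so whatever Bonferroni rejects, Holm rejects. If m0 nulls are true, the first of them can be rejected only at a threshold no larger than 0.05/m0. The chance of that is at most m0 × 0.05/m0 = 0.05, with no condition on dependence.

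**Step 4: size of the gain.** Simulation with 40,000 runs per setting, two-sided tests, 91 per group and effect 3/7. Each cell gives average power per true effect at correlation 0 / 0.5.

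| m | True effects | Bonferroni | Holm | Gain in points |
|---|---|---|---|---|
| 7 | 2 | 0.581 / 0.582 | 0.594 / 0.592 | 1.3 / 1.0 |
| 7 | 4 | 0.580 / 0.581 | 0.622 / 0.618 | 4.2 / 3.7 |
| 7 | 7 | 0.580 / 0.580 | 0.705 / 0.688 | 12.5 / 10.8 |
| 19 | 5 | 0.454 / 0.453 | 0.467 / 0.466 | 1.3 / 1.3 |
| 19 | 10 | 0.453 / 0.453 | 0.486 / 0.488 | 3.3 / 3.5 |
| 19 | 19 | 0.454 / 0.456 | 0.549 / 0.566 | 9.5 / 11.0 |
| 24 | 6 | 0.424 / 0.422 | 0.436 / 0.434 | 1.2 / 1.2 |
| 24 | 12 | 0.425 / 0.425 | 0.453 / 0.456 | 2.8 / 3.1 |
| 24 | 24 | 0.425 / 0.426 | 0.510 / 0.531 | 8.5 / 10.5 |

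Holm's simulated family-wise error was at most 0.050 in every setting, and Holm rejected everything Bonferroni rejected in every run.

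**Step 5: a related conflict.** These figures are two-sided, as in Sample size justification ("The test is two-tailed, which means that an effect in either direction will be interpreted"). The Table 2 footnote says otherwise: "All tests will be one-sided using alpha = 0.05 level of significance in accordance with the non-inferiority hypotheses". That changes the power figures but not the ordering of the two procedures.

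**The case against.** - **Bonferroni is valid and prespecified, so nothing is broken.** This stands. The Holm point is about efficiency and is not a defect in error control.
- **The gain is small.** Largely fair. With 25 outcomes, 86 per group, correlation 0.3 and effect 0.5, it is about 0.5 points with 3 real effects, 1.4 with 6 and 3.6 with 12; at effect 0.3 it is 0.2 to 0.7 points across those cases. Larger gains need most outcomes to respond. With systolic and diastolic pressure counted separately, 14 of the 25 are cardiovascular or blood measures, for which the Background reports inconsistent benefit and the Discussion insufficient evidence. The article does hypothesise benefit in every secondary domain, so the upper range cannot be excluded, but it should not be the headline.
- **A reader might infer that the plan contradicts its own divisor and breaks its 0.05 bound.** The documents do not support this. No divisor is stated, and Table 2 summarises methods without being named as the multiplicity family. If blood pressure and dynamometry are each split in two and costs set apart, Table 2 has 20 measures and the text 25. Testing 25 at 0.05/20 = 0.0025 gives a bound of 25 × 0.0025 = 0.0625, but that is a worst case for a count nobody has declared. Simulated under the global null, the error was 0.053 at correlation 0.3 and 0.041 at 0.5.
- **The analysis plan will fix the number of tests.** It may, and the missing number alone is no finding. The two outcome lists and the two ranks for costs, however, conflict inside the article.
- **Holm is not wholly free.** Bonferroni has simple matching simultaneous intervals and Holm does not. This stands but costs little, since the article plans only unadjusted 95% intervals.

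**Conclusion.** The point holds as two modest, separate improvements.

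Holm dominates Bonferroni whatever the family size, effect size or correlation. The size of the gain does depend on assumptions: about 1 to 4 points of average power per true effect if a quarter to a half of the effects are real, and about 9 to 13 if all are, for 91 per group and a standardised effect of 3/7. It would be too strong to say that Bonferroni is wrong here or that it discards secondary effects on a large scale.

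The inconsistency in the secondary set rests on the article's text alone and is the weightier part, because Holm cannot be applied without one fixed list either. Depending on the reading, the Bonferroni threshold lies between about 0.007 and 0.001, and illustrative power per test between 0.58 and 0.35.

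**What to change.** 1. In Analyses, name Holm step-down instead of Bonferroni for the secondary outcomes.
2. Make Table 2 match the text under Secondary outcomes: add total cholesterol, insulin, C-reactive protein, the single self-efficacy question and the Stanford scale, or state that a measure is descriptive only. In the same pass, settle waist:hip ratio (in the text, not in Table 2) and the cholesterol/HDL ratio and non-HDL cholesterol (in the Fig. 2 caption only).
3. State whether costs are secondary or tertiary, and whether the 24-week tests belong to the family.
4. Give the resulting number of tests, apply Holm to that one list, and state one sidedness throughout.

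This takes wording and a one-line change of procedure, with no extra participants or data. The only loss is simple simultaneous intervals matching the tests, which the article does not plan to report. The list should be fixed before the unblinded results are seen.
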